#### Effectiveness

Research questions related to the effectiveness of FASTb versus FASTr on the primary and secondary outcomes will be answered using co-variance analyses with a correction for multiple testing, with the pre-test (T1) score on the dependent variable as a covariate, the post-test (T2) and 6-month follow-up (T3) scores as the dependent variable, and the condition (FASTb or FASTr) as a factor. Dichotomous outcome variables will be tested with Chi-square analysis to compare the percentage of the FASTb and FASTr conditions. Recidivism data after two years (T4) will be analyzed using Kaplan Meyer and Cox survival analyses. Effect sizes will be computed as Cohen’s d, based on adjusted means and standard errors.

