### Setting

FAST is offered by de Waag, an outpatient forensic mental health care center with 12 treatment sites in the Netherlands. Clients are referred by the juvenile justice system or voluntarily by mental healthcare facilities, school care coordinators, or general practitioners. FAST therapist teams at six treatments sites, located in Almere, Amersfoort, Amsterdam, Den Haag, Leiden, and Utrecht approach participants for the study. Participants will be recruited between 14 and 2022 and June 2025.

**Table 1 Tab1:** Concepts, instrument, and informants at the different assessment points

Variable type	Instrument	Respondent					Assessment				
		Ju	Ca	Th	CF	JR	T1	M	T2	T3	T4
Primary outcome	YSR	x					x	x	x	x	
	CBCL		x				x	x	x	x	
	SDB	x					x	x	x	x	
	Out of home placement (case file)*				x		x		x		
	Out of home placement questionnaire	x	x						x	x	
	RAF GGZ Youth*				x		x		x		
	Convictions					x					x
Secondary outcome	Peilstation Middelengebruik	x					x		x	x	
	Substance use questionnaire	x						x			
	RAF GGZ Youth*				x		x		x		
	FAST Goal lists*				x		x		x		
	BPQ	x					x	x	x	x	
	FAST Goal lists*				x		x		x		
Mechanism of change	PSQ		x				x		x	x	
	NRI	x	x				x	x	x	x	
	IPPA	x					x	x	x	x	
	NPSI		x				x	x	x	x	
	NPQ	x	x				x	x	x	x	
	Parenting Practices	x	x				x	x	x	x	
	PDI	x	x				x	x	x	x	
	PCS-YR	x					x	x	x	x	
	BITI	x			x		x	x	x		
Moderator	Demographic questionnaire	x	x	x			x				
	ICU	x	x				x				
	APSD	x	x				x				
	Primary diagnosis (case file)				x		x				
	RAF GGZ Youth*				x		x				
	FAST evaluation form*				x				x		
	Treatment time registration				x				x		
	Direct treatment time		x					x			
	Relationship with Interventionist	x	x					x	x		
	TMS-F	x	x				x		x		
	PETS		x				x				
	Cooperation Scale	x	x	x					x		

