##### Recidivism risk

Recidivism risk will be measured at T1 and T2 using the RAF GGZ Youth [39], which is filled out by therapists as part of the standard FAST procedure. Recidivism risk is rated on a 5-point Likert scale ranging from 1 = *low* to 5 = *high*.

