##### Recidivism

Recidivism will be measured at T4 by coding if, when, and what type of crime juveniles were convicted for from official judicial records.

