### Plan of data analysis

Data will be analyzed according to the intention-to-treat principle and will also be analyzed separately for the completers only. Little’s test will be used to test whether data is missing at random. If so, missing data will be imputed so that all participants can be included in the analyses. Possible baseline differences in demographic characteristics between the participating and non-participating FAST-clients will be checked by means of chi-square analyses and independent t-tests to investigate the representativity of the included sample. In addition, possible baseline differences in demographic characteristics and outcome variables between the FASTb and FASTr condition will be checked by means of (M)ANOVA (continuous variables) and chi-square analyses (categorical variables). If (some of) these variables show significant differences between FASTb and FASTr conditions, they will be entered as covariates in all (regression) models testing the effectiveness of the intervention.

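### No baseline risk measure is fixed in advance for the Cox analysis of two-year recidivism; the T1 risk rating enters only after a significant baseline difference between arms

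*Protocol article*

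**What the plan says.** The Effectiveness section of the protocol article treats its outcomes differently. Score outcomes are analysed by covariance analysis "with the pre-test (T1) score on the dependent variable as a covariate". For convictions the text is "Recidivism data after two years (T4) will be analyzed using Kaplan Meyer and Cox survival analyses", with no covariate named.

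Plan of data analysis adds a general rule. It states that "possible baseline differences in demographic characteristics and outcome variables between the FASTb and FASTr condition will be checked", and that where variables differ significantly, "they will be entered as covariates in all (regression) models testing the effectiveness of the intervention". A Cox model is a regression model, so the rule reaches it.

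On what is collected:
- The Recidivism section describes "coding if, when, and what type of crime juveniles were convicted for from official judicial records". Table 1 lists convictions at T4 only.
- The Recidivism risk section states "Recidivism risk will be measured at T1 and T2 using the RAF GGZ Youth [39], which is filled out by therapists", on a five-point scale.
- Under Inclusion and exclusion criteria, a medium to high rating on the same instrument is required for entry.
- The Setting section says "Clients are referred by the juvenile justice system or voluntarily by mental healthcare facilities", among other voluntary routes.

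**The concern.** The sample mixes justice-referred and voluntary clients, so the hazard of conviction is likely to vary between juveniles whatever the arm. The trial rates this risk before treatment, yet whether the rating enters the Cox model depends on a significance test of baseline balance. That is the wrong trigger: the value of adjusting comes from how strongly a variable predicts conviction, not from whether chance has made the arms differ on it.

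In a Cox model, leaving out a strong predictor moves the HR towards 1 and loses power even when the arms are perfectly balanced. The hypothesis is equal effectiveness, and the Conclusion turns on whether blended treatment is at least as effective. If a real difference existed, it would therefore be somewhat harder to see, on an outcome that the Discussion singles out for its relevance to authorities.

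**Working it through.** The article states no event count, HR or power for recidivism, so there is no figure to reproduce. Its sample-size calculation rests on a MANOVA and does not bear on this point.

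**1. How often the rule admits the rating.** Allocation is randomised 1:1 (Procedure). Assume a 5% baseline test. Under randomisation any baseline difference is chance, so

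P(rating enters) = 0.05 and P(rating left out) = 1 − 0.05 = 0.95.

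Prior conviction could not be screened at all, since Table 1 gives convictions no baseline value.

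**2. How much information the outcome carries.** Assume a true HR of 0.6, two-sided alpha 0.05 and power 0.80.
- Schoenfeld: events = 4(1.96 + 0.842)² / (ln 0.6)² = 4 × 7.85 / 0.261 = 120.3, so 121.
- Freedman: (1.6/0.4)² × 7.85 = 125.6, so 126.
- With 200 juveniles and an assumed 30-50% overall event share: 0.30 × 200 = 60 and 0.50 × 200 = 100 events.
- Power = Φ(0.511 × √events / 2 − 1.96). At 60 events this is Φ(0.02) = 51%; at 100 events it is Φ(0.59) = 72%.

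On these assumptions the outcome is short of events, so a gain that needs no extra participants is worth having.

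**3. What a fixed risk covariate changes.** Simulation: 100 per arm, exponential times, censoring at two years, one standard-normal risk score, 2,000 runs per setting, two-sided 5% Wald test. The true conditional HR is 0.6. All inputs except the sample size and allocation are assumptions. The event rate is set in the control arm, so the total number of events is about 50 or 85-87.

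| Control-arm event rate | Risk HR per SD | HR unadjusted | HR adjusted | Shift | Power unadjusted | Power adjusted | Gain (points) |
|---|---|---|---|---|---|---|---|
| 30% | 1.5 | 0.601 | 0.592 | 0.009 | 40.7% | 42.8% | 2.1 |
| 30% | 2.0 | 0.624 | 0.602 | 0.022 | 35.5% | 39.9% | 4.4 |
| 30% | 2.5 | 0.636 | 0.594 | 0.042 | 33.8% | 42.6% | 8.8 |
| 50% | 1.5 | 0.614 | 0.599 | 0.015 | 60.2% | 63.8% | 3.6 |
| 50% | 2.0 | 0.631 | 0.594 | 0.037 | 55.0% | 65.0% | 10.0 |
| 50% | 2.5 | 0.656 | 0.595 | 0.061 | 49.7% | 66.5% | 16.8 |

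Near 50%, the simulation error of one power figure is √(0.5 × 0.5 / 2000) = 1.1 points, so the smallest gain is slight.

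**4. The same check at a true HR of 1.** Both HRs average 0.99-1.00 and rejection is 4-5% in both models. The standard error of the log HR is the same with and without the covariate: 0.26 at a 30% event rate and 0.20 at 50%. Here adjustment neither moves the estimate nor narrows the interval.

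**5. Where in the range the trial probably lies.** The simulated score is continuous, perfectly measured and unrestricted. The RAF rating is a five-point therapist judgement among juveniles already selected for medium-to-high risk, so its spread is narrowed. That points to the rows with HR 1.5 per SD: a shift of about 0.01-0.02 and a gain of about 2-4 points.

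**The case against.** The strongest reply has four parts.

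**The plan does not exclude entry risk.** A reader might infer that recidivism is analysed without any measure of risk at entry. The text does not support that: the T1 RAF rating is itself an outcome variable, and the general rule admits it to the Cox model if the arms differ significantly. This part stands. What remains is that adjustment is conditional when it could be fixed.

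**Covariate lists are commonly left to an analysis plan.** A full plan is not shown and may name Cox covariates. But the article is not silent here. It states one fixed rule for scores and one significance-triggered rule for other covariates, and the criticism is of that stated rule.

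**The HR is not biased.** Under randomisation the unadjusted HR validly estimates the marginal effect, and the shift is non-collapsibility. A reader might also infer that the plan is tilted towards finding equal effectiveness. At HR = 1, the trial's own hypothesis, there is no attenuation. The worry arises only if the arms truly differ and a non-significant result is read as equivalence, which is a separate matter. This part stands.

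**The covariate may be weak or badly timed.** Range restriction limits the gain, as shown above. T1 may fall in the first weeks of treatment, and Table 2 also places the establishment of risk in the pre-treatment stage. By then the therapist may know the allocation, so a rating coded as T1 is not guaranteed to precede it. This part stands and shapes the fix.

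It would also go too far to say that first convictions and re-convictions cannot be separated. The article does not say whether the judicial extract reaches back before randomisation.

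**Conclusion.** The point holds in a limited form. For one of several primary outcomes, no baseline risk measure is fixed in the Cox model, and the stated rule leaves the available risk rating out about 95% of the time. Fixing the covariate in advance is the better method.

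The size depends on inputs that the article does not give. Over the assumed range the HR shift is about 0.01-0.06 and the power gain about 2-17 points, probably at the low end. Adjusted power for HR 0.6 is still only about 40-67%, so adjustment improves this analysis without making up for the shortage of events. If the true HR is 1, nothing is lost by leaving the covariate out. This is a cheap improvement, not a defect that invalidates the analysis.

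**What to change.** Prespecify the Cox model as condition plus the RAF GGZ Youth recidivism-risk rating (1-5), using the rating made at intake for eligibility and before randomisation. Keep it in the model whatever the baseline comparison shows. Report the unadjusted HR beside the adjusted one.

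Add prior conviction (yes/no) only if the judicial extract contains convictions dated before randomisation. The article does not settle this, so it should be checked with the data request. If it does not, use the RAF rating alone.

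Cost: a sentence of model wording, retrieval of the intake rating from the case file and, if available, one extra coded field from records already being requested. No extra participants are needed. The one small downside is that the adjusted HR is conditional on entry risk and must be labelled as such, since it estimates a different quantity from the unadjusted HR.

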#### Sample size calculation

Based on a MANOVA a priori power analysis, a group of *n* = 120 (*n* = 60 per group) will allow us to identify – with a power of 0.80, an alpha of 0.05 – small differences (d = 0.15) in effectiveness between FASTb and FASTr (G*power 3.1) [40]. To account for possible drop-out, which was approximately 20% in our previous comparable study [41], *n* = 200 participants will be recruited. Based on the number of juveniles referred to FAST at the treatment sites participating in this project (approximately 120 juveniles yearly), and participation rates of 70–90% in our earlier comparable studies [41, 42], it is considered feasible to include in total *n* = 200 juveniles and their caregivers within three years.

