#### Moderation

The research questions related to the moderators (demographics, juvenile and caregiver psychopathology, social support, and treatment characteristics) will be answered by including an interaction term (moderator*condition) to the model with a correction for multiple testing. Post-hoc analyses for moderator effects will be conducted by splitting the file according to the moderator and again conducting an ANCOVA and calculating effect sizes separately for each group. Regression analyses will be conducted for the continuous moderators, and multi-group analyses will be performed for dichotomous variables.

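### Cohen's d built from ANCOVA-adjusted means and standard errors is most naturally read as a residual-SD effect size, larger than a conventional d and not comparable across outcomes, time points or subgroups

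*Protocol article*

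**What the plan says.** The Effectiveness section of the protocol article plans analyses of covariance, "with the pre-test (T1) score on the dependent variable as a covariate", with the T2 and T3 scores as dependent variables and condition as the factor. It then defines the effect size as a Cohen's d "based on adjusted means and standard errors". It names no standardising SD and does not say how a standard error becomes an SD.

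Four other statements bear on the point:

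- Plan of data analysis: demographic or outcome variables that differ significantly between the arms at baseline are added to the models. In the article's words, "they will be entered as covariates in all (regression) models testing the effectiveness of the intervention".
- Moderation: post-hoc work splits the file by the moderator, reruns the ANCOVA and proceeds by "calculating effect sizes separately for each group".
- Effectiveness, for other outcome types: "Dichotomous outcome variables will be tested with Chi-square analysis to compare the percentage of the FASTb and FASTr conditions", and "Recidivism data after two years (T4) will be analyzed using Kaplan Meyer and Cox survival analyses".
- Sample size calculation: the planning effect is expressed on a d scale, as "small differences (d = 0.15) in effectiveness between FASTb and FASTr".

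**The concern.** Cohen's d is conventionally a mean difference in units of the ordinary between-person SD. The two inputs named in the article do not deliver that unit unless a further step is taken. The adjusted means give a sound numerator. The standard errors that accompany them reflect residual variance only, so an SD recovered from them is too small by a factor that depends on how well T1 predicts the outcome.

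The loss of a common unit matters more than the size of any single d:

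- **Across outcomes.** Scales with a strong T1-outcome correlation would show larger d values than scales with a weak one, for the same difference in ordinary SD units.
- **Between T2 and T3.** T3 comes six months after treatment ends. If r is lower at T3 than at T2, a constant difference would look as if it were fading. The Discussion of the article wants to detect sleeper effects, and this artefact could mask one.
- **Between subgroups.** In the split-file analyses each subgroup supplies its own residual SD. Equal raw differences could then look like moderation.
- **With chance imbalance.** Covariates enter only if they happen to differ at baseline. Those that predict the outcome shrink the residual SD further, so the unit of d depends on the randomisation draw.

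The article expects the two versions to be equally effective, and readers will look at effect sizes to see how far apart the arms are.

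**Working it through.** **Plan's own figure.** The article states no outcome SD, no pre-post correlation and no expected adjusted d, so there is nothing to reproduce. The check is on the mechanism.

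**Inputs**

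- Model: ANCOVA with T1 as covariate (Effectiveness).
- Inputs to d: adjusted means and their standard errors (Effectiveness).
- Arm sizes: 60 per arm in the power statement, 100 per arm randomised, and 80 per arm after about 20% dropout, since 100 × 0.80 = 80 (Sample size calculation).
- r, the within-arm correlation of T1 with the outcome: not in the article, so it is assumed and varied.

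**Step 1. What the standard error contains.** With residual SD s_res, the adjusted mean in arm j has

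SE² = s_res² × [1/n_j + (x̄_j − x̄)² / SS_x].

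Under randomisation the second term is small, so SE × √n ≈ s_res.

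**Step 2. Residual SD against raw SD.** With one covariate, s_res ≈ SD × √(1 − r²). For the same adjusted difference,

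d(from SE) / d(raw SD) = 1/√(1 − r²).

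**Step 3. Numbers.** The last column applies the ratio to a raw-SD d of 0.30, chosen only for illustration.

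| assumed r | 1/√(1 − r²) | excess | 0.30 would be reported as |
|---|---|---|---|
| 0.1 | 1.005 | 0.5% | 0.30 |
| 0.3 | 1.048 | 4.8% | 0.31 |
| 0.5 | 1.155 | 15.5% | 0.35 |
| 0.6 | 1.250 | 25.0% | 0.38 |
| 0.7 | 1.400 | 40.0% | 0.42 |
| 0.8 | 1.667 | 66.7% | 0.50 |

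**Step 4. Simulation.** 4,000 replicates per setting, true raw-SD d = 0.30, SD recovered as SE × √n. Results with 80 per arm:

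| assumed r | mean d from SE | mean d from raw SD | mean ratio of SDs |
|---|---|---|---|
| 0.3 | 0.320 | 0.306 | 1.05 |
| 0.5 | 0.347 | 0.300 | 1.15 |
| 0.7 | 0.425 | 0.303 | 1.40 |

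The ratios are nearly the same with 60 and with 100 per arm, so this is not a small-sample effect. Dividing by the raw pooled SD removes it.

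**Step 5. Comparability, using the Step 3 values.**

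- If r were 0.7 at T2 and 0.5 at T3, a constant raw-SD d of 0.30 would be reported as 0.42 and then 0.35.
- If r were 0.3 in one subgroup and 0.7 in the other, the same d of 0.30 in both would be reported as 0.31 and 0.42.

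These pairs of r are assumptions that show the size of the artefact. They are not estimates for this trial.

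**The case against.** The strongest reply is that the article never states a divisor. It names adjusted means and standard errors, and an analyst could back-transform to the raw SD using r. A condensed article may also leave computational detail to the analysis plan. The first half stands: the residual-SD divisor is an inference. The second half does not dispose of the point. The article does not leave the formula open. It names its inputs, and those inputs used directly give the residual-SD version. No back-transformation is mentioned.

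Some stronger conclusions that a reader might draw are not supported:

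- **That every effect size is affected.** Out of home placement is coded no/yes and goes to chi-square, and T4 recidivism goes to Kaplan-Meier and Cox analysis. Neither analysis yields an ANCOVA-adjusted mean.
- **That the excess can be put at 15–40%.** That band needs r between about 0.49 and 0.70. The article gives no r, and below 0.49 the excess is under 15%.
- **That the trial judges equal effectiveness by how small d is.** No section sets a d threshold or decision rule. If readers did use d that way, an enlarged d would count against the trial's hypothesis, so the distortion would be conservative in that respect.
- **That the reported d is off the planning scale of 0.15.** The power analysis is described as a MANOVA, and 60 per arm does not reproduce as a two-group comparison at d = 0.15, which would need 698 per arm (two-sided). The scale of that 0.15 is therefore uncertain, and the comparison proves little.

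It is also true that extra covariates enlarge d only if they explain outcome variance, and that a fall in r from T2 to T3 is plausible but undocumented.

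**Conclusion.** The point holds for continuous outcomes analysed by ANCOVA. On the natural reading, d is inflated relative to a raw-SD Cohen's d by 1/√(1 − r²), and the direction is certain whenever r is not zero. The size cannot be fixed from the article: about 5% at r = 0.3, 15% at 0.5, 40% at 0.7 and 67% at 0.8.

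The conclusion rests on two assumptions: that the SD is recovered as SE × √n, and that the additional covariates do not change the picture much. Where such covariates do predict the outcome, the inflation is larger.

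The consequence is limited to reported standardised sizes and their comparability across outcomes, between T2 and T3, between moderator subgroups, and with conventional benchmarks. P-values, tests and sample size are untouched. It should still be corrected before results exist, because choosing the standardiser afterwards would be discretionary.

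**What to change.** Replace the effect-size sentence in the Effectiveness section with wording such as: *For continuous outcomes, Cohen's d is the ANCOVA-adjusted mean difference divided by one pooled unadjusted SD per outcome, taken from the total sample, and is reported with a 95% CI. The same SD is used at T2, at T3 and in all moderator subgroups.* Refer to this sentence from the Moderation section.

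The T1 SD is a suitable default. It is less suitable where eligibility narrows the T1 range. Recidivism risk is the clear case, because entry requires medium to high risk on the same instrument that measures the outcome. There, name the unadjusted outcome SD instead. The list of outcomes using each SD should be fixed in advance.

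If the team prefers the residual-SD version, it should at least be labelled as a covariate-adjusted d. That avoids misreading but does not restore comparability.

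The cost is one sentence, with no new data and no change to any test. The downside is that reported d values will generally be smaller.

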#### Mechanisms of change

The research questions related to the expected mechanisms of change (social support, family functioning, and cognitive distortions) will be investigated by testing whether changes in the hypothesized mechanism of change predict change in the primary and secondary outcomes.

#### Moderation

The research questions related to the moderators (demographics, juvenile and caregiver psychopathology, social support, and treatment characteristics) will be answered by including an interaction term (moderator*condition) to the model with a correction for multiple testing. Post-hoc analyses for moderator effects will be conducted by splitting the file according to the moderator and again conducting an ANCOVA and calculating effect sizes separately for each group. Regression analyses will be conducted for the continuous moderators, and multi-group analyses will be performed for dichotomous variables.

